## Abstract

**Background:**

With high morbidity, mortality and disability rate, brain infarction brings a huge economic and health burden to the whole society in China. Although some previous studies suggested that telerehabilitation may facilitate rehabilitation for stroke survivors at home, the evidence is insufficient for clinical application; additionally, as yet no trial evaluates efficacy of telerehabilitation for brain infarction patients. Therefore, more high quality trials are needed to provide practice evidence for this novel rehabilitation strategy.

**Methods/Design:**

Based on recruitment criteria, this assessor blinded, paralleled randomized controlled trial will recruit 210 brain infarction patients. After being randomly allocated into two groups, participants will receive home-based tele-supervising rehabilitation or conventional rehabilitation. Outcome measurement will be conducted at the end of intervention and 90-day follow-up. Among which, Barthel index assessment will be considered as primary outcome measurement, secondary outcome measurements include NIHSS score, mRS score, 3-oz water swallow test and surface electromyography. Adverse events will also be recorded during the whole process of the trial for safety assessment.

**Discussion:**

The HTRBIP trial will evaluate efficacy and safety of home-based tele-supervising rehabilitation for brain infarction patients. It is expected to provide new evidence for telerehabilitation application.

**Trial registration:**

Registration date: 17 September 2014; Registration number: ChiCTR-TRC-14005233

## Background

In China, there are 2.5 million new stroke patients each year and stroke has become a leading cause of adult death and disability [1-3]. It is estimated that stroke care annually costs nearly 40 billion RMB (6.35 billion US dollars) in China, which brings a huge health burden to the society [2]. Among different stroke types, the incidence of brain infarction is approximately twice that of hemorrhagic stroke; therefore, brain infarction may be a key element for solving the problem caused by stroke [4].

Although recombinant tissue plasminogen activator (rt-PA) has been approved as the fundamental therapy for thrombolysis, because of its utilization restrictions, the thrombolytic rate is still low [5,6]. Based on the report of the Chinese National Stroke Registry (CNSR), the rate of administration of intravenous rt-PA rate for acute brain infarction patients in China is merely 1.6% [7]; and more than half the survivors are frustrated by physical deficiency after discharge from hospital, which limits their daily activity and poses a heavy burden on their families [8]. Numerous clinical trials have demonstrated that physical rehabilitation can ameliorate neurological functional impairment and raise quality of life [9,10]. However, because of transportation restrictions and high costs, most brain infarction survivors in China cannot receive professional supervised rehabilitation, which restricts physical function recovery and delays the best rehabilitation time [11]. To resolve the problem, telerehabilitation, a novel rehabilitation strategy, has been put forward.

Telerehabilitation, which was first reported in late 1990s, can be defined as an alternative method for delivering rehabilitation services via a certain telecommunication system [12]. This novel rehabilitation strategy facilitates brain infarction survivors receiving long-term ongoing rehabilitation with supervision, especially for those who reside in remote areas and have hardly any access to rehabilitation expertise [13,14]. After being first reported in the late 1990s, telerehabilitation aroused wide interest. Several randomized controlled trials have demonstrated that compared with conventional rehabilitation care, telerehabilitation can improve physical function under remote guidance through a tele-consultant [15-17]. It also indicates that there are no differences between telerehabilitation and usual rehabilitation in patients’ satisfaction, comprehension of treatment, user-friendliness, and the patient-therapist relationship [18,19]; moreover, it may also reduce travel time, being more convenient for patients receiving rehabilitation guidance. Therefore, it seems that telerehabilitation can successfully encourage patients to persist with rehabilitation treatment and improve their physical function recovery.

Despite its advantages, clinical application for telerehabilitation is still limited. Based on a recent Cochrane study, more randomized controlled trials (RCTs) are needed to supplement clinical evidence for telerehabilitation application [20]. And because there is no clinical trial to evaluate telerehabilitation for brain infarction patients, our group will conduct an assessor blinded, randomized, paralleled controlled trial to investigate efficacy and safety of home-based tele-supervising rehabilitation for brain infarction patients, and further increase the experience gained from this novel rehabilitation strategy application.

## Methods and design

### Study objective

The main objective of the home-based tele-supervising rehabilitation for brain infarction patients (HTRBIP) trial is to investigate the efficacy and safety of home-based tele-supervising rehabilitation for patients after brain infarction. The specific study objectives are:Primary research question: compared with conventional rehabilitation care, will home-based tele-supervising rehabilitation improve daily living activity of brain infarction patients at the end of 90 or 180 days after intervention has been initiated?Secondary research question: compared with conventional rehabilitation care, will home-based tele-supervising rehabilitation improve neurological function of brain infarction patients at the end of 90 or 180 days after intervention has been initiated?Record physiological data and adverse events to investigate safety of home-based tele-supervising rehabilitation for brain infarction patients.

### Study design

The HTRBIP trial is an assessor blinded, paralleled RCT. Participants will be recruited in Shanghai Number 5 Hospital, Fudan University, Shanghai, China. After signing informed consents, eligible patients will receive baseline assessment, and then be randomized into the tele-supervising rehabilitation group or conventional rehabilitation group. Participants in both groups will receive rehabilitation intervention for 90 days; specific rehabilitation strategy in each group will correspond to the allocation. At the end of intervention and 90-day follow-up, a group of assessors blinded to allocation and intervention will measure the outcome. Meanwhile, adverse events will be recorded during the whole process of the trial. Figure 1 depicts simply the study design, and Table 1 shows the trial procedure.

**Figure 1 Fig1:**
[figure not shown]
**Flow chart illustrating the home-based tele-supervising rehabilitation for brain infarction patients (HTRBIP) trial design.**

**Table 1 Tab1:** **Process chart of home-based tele-supervising rehabilitation for brain infarction patients (HTRBIP) trial**

		**Time 1** ^**a**^ **: enrollment**	**Time 2** ^**b**^ **: baseline assessment**	**Time 3: intervention**	**Time 4** ^**c**^ **: at the end of intervention**	**Time 5** ^**d**^ **: 90- day follow-up**
**Informed consent obtained**		√				
**Epidemic data collection**		√				
**Medical history collection**		√				
**Physical examination**		√				
**Recruitment criteria assessment**		√				
**Randomized allocation**			√			
**Physiological data collection**	Body temperature		√	√		
	Respiratory rate		√	√		
	Pulse rate		√	√		
	Blood pressure		√	√		
	Surface electrocardiogram		√	√		
	Peripheral blood oxygen saturation		√	√		
**Primary outcome measurement** (Barthel index)			√		√	√
**Secondary outcome measurement**	NIHSS score		√		√	√
	mRS score		√		√	√
	3-oz water swallow test		√		√	√
	sEMG		√		√	√
**Adverse events record**			√	√	√	√

^a^Time 1: 2 to 7 days before intervention initiation.^b^Time 2: 0 to 2 days before intervention initiation.^c^Time 4: 90 days after intervention initiation.^d^Time 5: 180 days after intervention initiation.

Abbreviations: mRS, modified Rankin Scale; NIHSS, National Institute of Health Stroke Scale; sEMG, surface electromyography.

### Participant recruitment

Participant recruitment will be conducted in Shanghai Number 5 Hospital, Fudan University, Shanghai. Before discharge from hospital, each brain infarction patient will be identified by two independent neurologists according to inclusion and exclusion criteria. After being confirmed, eligible patients will receive a face-to-face meeting for exchanging the information of the study. If eligible patients accept and decide to participate in the study, they will be asked to sign the informed consent and follow the subsequent study process, which includes baseline assessment, randomized allocation, intervention receiving, and follow-up visiting. Informed consent from each participant should be obtained before baseline assessments.

### Sample measurement

Primary outcome of the study will be measured by using the Barthel index. The main purpose of the study is to investigate the efficacy of tele-supervising rehabilitation compared with conventional rehabilitation, and sample size calculation will be conducted by following formula:$$ {n}_1={n}_2=\frac{2{\left({z}_{a/2}+{z}_{\beta}\right)}^2{\sigma}^2}{{\left({\mu}_1-{\mu}_1\right)}^2} $$

According to the previous study, difference in means of 90-day post-stroke Barthel index is 7.8 and standard deviation is 18.35 [21]. Taking 5% 2-side significance level and 80% power into consideration, at least 87 participants need to be recruited in each group. For 20% attrition, our study will recruit 105 participants in each group.

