### Randomization and allocation concealment

After being recruited and having undergone baseline assessment, participants will be randomly allocated into either tele-supervising rehabilitation or conventional rehabilitation. Block randomization will be stratified by age (≤65 years old, > 65 years old) and NIHSS score (2 to 10, 11 to 20) with 1:1 allocation to each group. An independent statistician will conduct randomized allocation by using a computer. Allocation concealment will be ensured, as allocation information will be protected in opaque sealed envelopes by a specified staff member who is not involved in the study. Only after participant recruitment and baseline measurements are completed, will the envelopes be opened.

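### The recruitment target of 105 per arm does not cover the stated 20% attrition: it leaves 84 per arm, below the 87 required for 80% power

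*Protocol article*

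**What the plan says.** The section headed Sample measurement in the protocol article sizes the trial on the Barthel index. It takes from an earlier study that the "difference in means of 90-day post-stroke Barthel index is 7.8" and that the "standard deviation is 18.35". For the error rates it says "Taking 5% 2-side significance level and 80% power into consideration", and it concludes that "at least 87 participants need to be recruited in each group". The next sentence adds the allowance for loss: "For 20% attrition, our study will recruit 105 participants in each group".

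The Methods/Design part of the abstract carries the result forward as a total: "paralleled randomized controlled trial will recruit 210 brain infarction patients". Randomization is in equal proportions (Randomization and allocation concealment: "with 1:1 allocation to each group"), so 210 means 105 per group.

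**The concern.** Attrition is a share of those recruited. If 20% of recruited participants provide no outcome, 80% remain, so the number to recruit is the required number divided by 0.8. The figure of 105 looks instead like the required number multiplied by 1.2. That is a 20% mark-up on 87, and it covers a loss of less than 20% of those recruited.

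If so, the section contradicts itself: it sets a minimum of 87 per group, assumes a 20% loss, and chooses a target that falls below the minimum at that loss. The stated power would not be delivered at the stated attrition, and any later document that takes over these figures would inherit the mismatch. The article's Discussion also justifies the trial partly by the small samples of earlier telerehabilitation trials, so its own power statement should be right.

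**Working it through.** **Inputs** (all from Sample measurement, except the allocation ratio)

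- Difference in means: 7.8 points
- Standard deviation: 18.35
- Significance level: 5%, two-sided (z = 1.960)
- Power: 80% (z = 0.842)
- Attrition: 20%
- Allocation: 1:1 (Randomization and allocation concealment)

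**Step 1. Reproduce the 87.**

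n per group = 2 × (1.960 + 0.842)² × 18.35² / 7.8² = 86.88, rounded up to 87. This matches the article. The printed formula has the same mean twice in its denominator; that is an evident typing error and does not affect the result.

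**Step 2. Look for the source of 105.**

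- 87 × 1.2 = 104.4, rounded up to 105: matches.
- 87 / 0.8 = 108.75, rounded up to 109: does not match.

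Starting from the unrounded 86.88 changes nothing: × 1.2 gives 104.26 (105), and / 0.8 gives 108.60 (109).

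**Step 3. Apply the stated attrition to the stated target.**

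105 × 0.8 = 84 per group, which is 87 − 84 = 3 short.

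**Step 4. Find the attrition that 105 does cover.**

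1 − 87/105 = 0.171, or 17.1%.

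**Step 5. Power with 84 outcomes per group.**

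Standard error of the difference = 18.35 × √(2/84) = 2.831. Then 7.8 / 2.831 = 2.755, and power = Φ(2.755 − 1.960) = Φ(0.795) = 78.7%.

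| Outcomes per group | Power, normal approximation | Power, noncentral t |
|---|---|---|
| 84 | 78.7% | 78.2% |
| 87 | 80.05% | 79.6% |

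Within either method the loss from 87 to 84 is about 1.4 percentage points.

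**Step 6. Difference detectable with 80% power at 84 per group.**

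(1.960 + 0.842) × 2.831 = 7.93 points, against the 7.8 assumed.

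**Step 7. Check the consistent target.**

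109 × 0.8 = 87.2 per group, which meets 87. The total would be 2 × 109 = 218, eight more than 210.

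**The case against.** There are four fair points on the other side.

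- **The inflation formula is not printed.** Multiplication by 1.2 is inferred from the exact numerical match, and the sentence could be read loosely as a 20% margin added to 87. This stands as a caution about how the error arose. It does not remove the contradiction: under any reading, 105 less 20% is 84.
- **The analysis set is not 84.** The Statistics section includes all randomized participants on an intention-to-treat basis, with multiple imputation for missing data. The 84 and the 78.7% are therefore complete-case approximations. Imputation may recover part of the loss if the observed data predict the missing outcomes well, but the article gives no figure for this, and imputation does not in general restore the missing information. The plan itself added participants for attrition, so it treats loss as reducing the effective sample size.
- **The effect is minor.** It is smaller than the uncertainty in the inputs. At 84 per group, power is back to about 80% if the standard deviation is 18.05, and falls to about 76% if it is 19. This stands, and it limits the weight of the point, but it does not make the stated figure right.
- **The choice of method matters at this scale.** By noncentral t, 87 per group already gives slightly under 80% (88 would be needed), so the t-based 78.2% should be compared with 79.6%, not with 80%. This stands; the normal approximation is the like-for-like basis because the article's own formula uses it.

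**Conclusion.** The point holds. The stated requirement (87), attrition (20%) and target (105 per group, 210 in total) cannot all be true: 105 per group leaves 84 after the stated loss. At that loss power is about 78.7% instead of 80%, the detectable difference is 7.93 instead of 7.8 points, and the target keeps the required 87 only up to 17.1% attrition.

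This is a small but certain error in a stated figure. It does not make the trial seriously underpowered. The contradiction itself needs no assumption beyond reading attrition as a share of those recruited. The power figures also assume the article's difference and standard deviation, the normal approximation, and that participants without an outcome contribute no information.

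**What to change.** Keep the target of 210 and correct the sentence in Sample measurement, for example: *With 105 participants per group and 20% attrition, 84 per group are expected to provide outcome data, giving about 79% power to detect a 7.8-point difference (standard deviation 18.35, two-sided 5% level); 80% power is retained if attrition does not exceed about 17%.* The abstract's total then needs no change, and the analysis plan and trial report should use the corrected statement. The cost is one sentence and a slightly less favourable power figure, with no extra participants.

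The alternative is to state 109 per group (218 in total). That restores the 80% claim by the article's own formula, but it changes the target of a trial that, according to Trial status, is already recruiting, for a gain of about 1.4 percentage points at 20% attrition. The restated sentence is the more proportionate choice.

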### Inclusion criteria

Patients will be eligible for inclusion if they meet all the following criteria: 1) be aged 35 to 85 years old, male or female; 2) be first diagnosed as brain infarction or have historical brain infarction but without neurological function impairment; 3) be 14 to 90 days from brain infarction onset; 4) have National Institute of Health Stroke Scale (NIHSS) scores from 2 to 20, modified Rankin Scale (mRS) scores from 1 to 4; 5) have not previously received any rehabilitation intervention.

### Exclusion criteria

Patients will be excluded if they meet any of following criteria: 1) have Glasgow Coma Scale (GSC) scores under 15, have been confirmed as having dementia based on Minimum Mental State Examination (MMSE) assessment, with mental disorders and unable to cooperate with examination, treatment or follow-up; 2) have disability not induced by brain infarction or disability induced by historical brain infarction; 3) have associated severe primary disease of heart, liver, kidney or hematological system; 4) have cognitive disorder, history of psychosis, substance abuse or alcoholism; 5) have skin infections in the antebrachium or crus; 6) have associated hemorrhagic or skin ulceration tendency; 7) have metal implants in the body, including cardiac pacemaker, metal stent or steel plate; 8) be in the gestation or lactation period or have a fertility plan; 9) have associated malignant tumor or severe progressive disease in any other system; 10) have been recruited by any other clinical trial in the preceding 90 days; 11) be unable to complete the basic course of treatment, with poor treatment adherence or inability to follow-up; 12) have other conditions that render them unable to continue the trial.

### Randomization and allocation concealment

After being recruited and having undergone baseline assessment, participants will be randomly allocated into either tele-supervising rehabilitation or conventional rehabilitation. Block randomization will be stratified by age (≤65 years old, > 65 years old) and NIHSS score (2 to 10, 11 to 20) with 1:1 allocation to each group. An independent statistician will conduct randomized allocation by using a computer. Allocation concealment will be ensured, as allocation information will be protected in opaque sealed envelopes by a specified staff member who is not involved in the study. Only after participant recruitment and baseline measurements are completed, will the envelopes be opened.

### Blinding

Because tele-supervising rehabilitation needs the use of a specific device for computer-based tele-consultation, it is impossible to blind the patients and tele-supervising rehabilitation therapists to allocation and intervention. In order to reduce bias, outcome assessment and data analysis will be carried out by an independent neurologist and a statistician respectively; both of them are blinded to allocation, baseline measurements, and rehabilitation intervention.

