### Statistics

An independent statistician, who is blind to allocation and intervention, will take charge of data analysis. All the variables will be analyzed according to an intent-to-treat (ITT) basis, and the statistical tests will be 2-side and at the 5% significance level. All the participants under randomization will be included in the analysis, regardless of whether or not they adhered to the treatment or provided complete data sets. For providing valid inferences with less restrictive assumptions, multiple imputation will be performed to analyze missing data. Continuous variables will be summarized by means and standard deviation. The normality of the distribution will be checked before comparison by using the Shapiro-Wilk test. Normally distributed variables will be compared by using the *t*-test, and the Mann-Whitney *U-*test will be performed to compare non-normally distributed variables. Discrete variables will be summarized by relative frequencies and analyzed by using a non-parametric test. The level of statistical significance will be set at *P* < 0.05. SAS V9.1 (SAS Institute, Cary, NC, USA) will be employed for all the statistical analysis. The statistical analysis plan will be fully specified and approved before unmasking.

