The HTRBIP trial is designed as an assessor blinded, paralleled RCT. Tele-supervising rehabilitation will be conducted through a specialized system that can connect therapist and patient over distance; data collecting will be simultaneously performed during rehabilitation. Barthel index at the end of intervention and at 90-day follow-up will be evaluated as primary outcome measurement, which represents the general physical function for disabled patients after brain infarction. NIHSS score, mRS score, 3-oz water swallow test and sEMG will be employed for secondary outcome measurement. Furthermore, adverse events will be recorded for safety evaluation. For tele-supervising rehabilitation specialized remote interaction devices are required, and because it is impossible to blind the intervention strategy to the patients and therapists, this trial could not be double-blinded. To make up for this limitation and ensure the quality of the trial, outcome assessors and data statisticians will be blind to the allocation and intervention strategy.

The HTRBIP trial will evaluate efficacy and safety of home-based tele-supervising rehabilitation for brain infarction survivors in China, which is expected to supplement evidence for telerehabilitation application, and increase the experience gained for its practice.

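### The Blinding section withholds baseline measurements from the analysing statistician; this conflicts with the Statistics and Discussion sections and, read literally, weakens the planned multiple imputation with no gain in protection.

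*Protocol article*

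**What the plan says.** The Blinding section of the protocol article assigns outcome assessment to an independent neurologist and data analysis to a statistician, then states that "both of them are blinded to allocation, baseline measurements, and rehabilitation intervention". The statistician is therefore expressly included.

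Two other places describe the statistician's blinding without mentioning baseline:

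- Statistics: "An independent statistician, who is blind to allocation and intervention, will take charge of data analysis".
- Discussion: "outcome assessors and data statisticians will be blind to the allocation and intervention strategy".

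On analysis, the Statistics section commits to this: "All the participants under randomization will be included in the analysis, regardless of whether or not they adhered to the treatment or provided complete data". It adds that "multiple imputation will be performed to analyze missing data". Arms are compared by t-test or Mann-Whitney test. The section states no covariate adjustment and names no imputation predictors.

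Baseline Barthel, NIHSS, mRS, swallow test and sEMG are recorded before allocation (Baseline assessment; Data measurement; Randomization and allocation concealment). Age and baseline NIHSS are the stratification factors. The same five measures are scheduled again only at day 90 and day 180 (Table 1).

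**The concern.** Keeping baseline scores from an outcome assessor is sensible, since knowing the starting score can anchor the later rating. The reason does not carry over to a statistician, who rates nobody. What threatens an analyst's neutrality is knowledge of the arms, and coded arms deal with that.

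Applied to the statistician, the rule works against the imputation commitment. Multiple imputation corrects for selective dropout only through variables that predict both the dropout and the missing value. For functional outcomes after stroke, the baseline functional scores are the natural candidates. They are also the only scheduled functional assessments for a participant who attends neither outcome visit.

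Selective dropout is plausible here. The plan allows for 20% attrition, the conventional arm attends outpatient therapy every day, and the Background says that "because of transportation restrictions and high costs, most brain infarction survivors in China cannot receive professional supervised rehabilitation".

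**Working it through.** **1. The statements on the statistician's blinding, side by side**

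| Section | Allocation | Intervention | Baseline measurements |
|---|---|---|---|
| Blinding | blinded | blinded | blinded |
| Statistics | blinded | blinded | not mentioned |
| Discussion | blinded | blinded | not mentioned |

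The Blinding section is the only one that adds baseline. It does so in a clause that covers assessor and statistician together, so wording meant for the assessor may have been extended by accident.

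**2. Does the extra restriction protect anything?** Baseline assessment precedes randomization, and the envelopes are opened only after baseline measurements are complete. A value fixed before allocation carries no information on the arm beyond chance imbalance. Withholding it adds nothing to masking.

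**3. How many participants could be affected?** Inputs from Sample measurement: difference 7.8, SD 18.35, two-sided 5%, power 80%, attrition 20%, 105 per group.

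- The plan's own figure: n = 2 × (1.960 + 0.842)² × 18.35² / 7.8² = 86.88, so 87 per group. This reproduces.
- Total recruited: 2 × 105 = 210. Outcomes missing at the planned attrition: 0.20 × 210 = 42.
- The split between one missed visit and two is not given, so the number missing both lies between 0 and 42 if attrition is as planned.

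**4. What remains for imputation under the literal rule?**

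- One visit missed: coded arm, the other visit's outcomes, physiological data during therapy, adverse events.
- Both visits missed: coded arm, physiological data during therapy, adverse events. The last two are likely weak predictors of the Barthel index, and sparse for anyone who leaves early.

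**5. What does that do to an arm mean?** Let p be the share missing both visits, m_c the mean of those observed and m_d the unobserved mean of those missing. In the limiting case where only arm predicts, the imputed mean is (1 − p) × m_c + p × m_c = m_c in expectation. That is the complete-case mean, and its bias is p × (m_c − m_d). If baseline explains a fraction f of the gap, access to it removes f × p × (m_c − m_d). That product is the part due to withholding baseline. The article gives none of p, the gap or f, so it cannot be computed.

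**6. What does the closed option of adjustment amount to?** This is illustration only, since no adjusted analysis is planned and the baseline-outcome correlation r is assumed. Adjustment reduces the SD to 18.35 × √(1 − r²).

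| Assumed r | n per group for 80% power | Power with 84 completers per group (105 × 0.8) |
|---|---|---|
| none (unadjusted) | 87 | 79% |
| 0.3 | 80 | 82% |
| 0.5 | 66 | 89% |
| 0.7 | 45 | 97% |

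**The case against.** The strongest reply is that one clause is being treated as a settled rule. The Statistics section, which governs the analysis, leaves baseline out of the statistician's blinding, and so does the Discussion. This stands: the document does not establish that the analyst will work without baseline data. It contains two statements that must be reconciled.

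Other parts of the reply also hold:

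- The planned comparisons are unadjusted, so no stated analysis is defeated. The rule only closes an option.
- A reader might infer that imputation would have nothing to work with. That goes too far, given the predictors listed in step 4. The boundary of baseline is itself unclear: Table 1 places the collection of epidemiological data and the eligibility checks at enrollment, while the Baseline assessment section lists age under baseline. Age and the eligibility scores might therefore escape the restriction.
- The Statistics section foresees an unmasking after the analysis plan is approved. It does not say what is unmasked, or whether the baseline restriction ends then.
- The case for dropout that differs by arm is plausible but not shown. Both arms attend the same outpatient department for outcome visits, exclusion criterion 11 removes patients unable to complete treatment or be followed up, and the Background remark concerns survivors in China generally.

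The reply that imputation predictors belong in the analysis plan answers a different complaint. Their absence from the article is no fault. The fault is a stated rule which an analysis plan using baseline data would have to contradict.

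**Conclusion.** The point holds as an inconsistency with a practical consequence. The Blinding section states a restriction on the statistician that two other sections do not share. Followed literally, it removes the strongest available predictors from an imputation meant to cover every randomized participant, and it protects nothing in return. It bears hardest on participants with no outcome visit, at most about 42 of 210 if attrition is the planned 20%. That baseline Barthel, NIHSS and mRS are the strongest predictors is a judgement, not a figure in the article.

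The size of the bias cannot be stated. A reader might assume that 20% of one arm drop out with Barthel scores 10 to 20 points below completers, obtain 0.2 × 10 = 2.0 to 0.2 × 20 = 4.0 points, and read 2.0/7.8 = 26% to 4.0/7.8 = 51% of the planning effect as the cost of this rule. The document does not support that reading. The gap is assumed, and the result is the total dropout bias in one arm's mean rather than the part that baseline would remove. It also reaches the treatment contrast in full only if the other arm has no such loss; equal loss in both arms would cancel. Nor does the document show in which direction any bias would run.

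**What to change.** In the Blinding section, limit blinding to baseline measurements to the outcome assessor. State there, in agreement with the Statistics and Discussion sections, that the statistician is blinded to allocation and intervention, works with coded arms (A/B) and has the full baseline data. In the analysis plan, include arm, baseline Barthel index, NIHSS, mRS, age and the other visit's outcome in the imputation model.

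The cost is one sentence in the protocol plus wording in the analysis plan. All these data are already scheduled for collection, no visit or measurement is added, and allocation masking is unchanged.
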